### Description of the Tests

Introspective sleepiness was investigated through the Karolinska Sleepiness Scale (KSS), a subjective scale assessing the level of sleepiness during the past 10 minutes [43]. Participants are required to rate their ability to maintain wakefulness on a Likert scale (from 1 = “perfectly awake” to 9 = “severely somnolent, cannot stay awake”). This score is known to correlate well with EEG measurements and cognitive and behavioral performances linked to the candidate’s ability to maintain wakefulness [44].

The ability to stay awake under sleep-promoting conditions was monitored through the MWT, which is considered the gold standard in the measurement of manifest sleepiness [18,45]. The MWT is a 40-minute trial during which the participant is in a comfortable position in bed, in a quiet, dimly lit room. At the beginning of each trial, the candidate is instructed to stay awake and combat against sleep, to keep their eyes open, and to look straight ahead, without looking at the light. During the test, visual analysis of the polysomnographic recording allows for monitoring the participant’s state, and the test is stopped when unequivocal sleep is detected (defined by 3 consecutive epochs of stage N1 sleep or 1 epoch of any other sleep stage, according to the American Academy of Sleep Medicine (AASM) recommendations [46]).

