The Vigilance Test of Attentional Performance (TAP) is a rarely used animated line test, which measures the ability to focus and to maintain mental effort and vigilance on a monotonous task during a 30-minute period [55]. The test displays a horizontal line going up and down on a screen at an irregular speed, and from time to time, this line oscillates with a greater amplitude. TAP Vigilance (Psytest) software was installed on a desktop computer running under Windows 10 and equipped with a specific external response button. The participant is asked to push the response button when they notice a difference in the line oscillation amplitude (target).

Finally, mind-wandering during completion of the test was assessed through a subjective scale, the Conscient Experience Characterization (CEC) [56]. At the end of the cognitive tests, participants were asked to rate their focusing level during the previous task, using a scale of five options: (1) fully focused (attention and thoughts entirely dedicated to the task), (2) focus interference related to the task (attention and thoughts distracted by task characteristics or by their performance), (3) external distraction (attention and thoughts distracted by environmental stimuli with no relation to the task), (4) mind wandering (not focused, with thoughts disconnected from the task or the environment), and (5) empty mind (not focused, without any particular thoughts).

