Driving performance, assessed using a driving simulator, is quantified by the variability of the car’s lateral position (standard deviation of lateral position [SDLP; cm]), indicating weaving of the car, and the number of inappropriate crossings of lateral highway lane markers (Inappropriate Line Crossing).

Cognitive performance is assessed using the PVT, the CPT, and the TAP. For the PVT, outcome measures include mean reaction time (RT; milliseconds), the fastest and slowest 10% of RTs, and the number of lapses (RT>500 ms). For the CPT, outcomes consist of the mean RT (measuring the response execution process), the number of omissions (failure to respond to target stimuli), and commission errors (responses given to nontarget stimuli). For the TAP, outcomes include mean RT and the number of omissions (missed targets).

Subjective sleepiness and mind wandering are assessed using the KSS and the CEC, respectively. The outcome measure for both is the score on the corresponding scale.

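### The mind-wandering outcome is defined as the CEC score, but the 1-5 codes are largely categories and a higher code does not mean more mind wandering

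*Protocol article*

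**What the plan says.** Under Description of the Tests, the protocol article introduces the CEC as a rating of focus: "participants were asked to rate their focusing level during the previous task, using a scale of five options". Option 1 is full focus on the task. The other four are:

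- Option 2, where the source of distraction is the task: "2) focus interference related to the task (attention and thoughts distracted by task characteristics or by their performance".
- Option 3, where the source is the surroundings: "3) external distraction (attention and thoughts distracted by environmental stimuli with no relation to the task".
- Option 4, the only one that carries the name of the outcome: "4) mind wandering (not focused, with thoughts disconnected from the task or the environment".
- Option 5, likewise a loss of focus but without thought content: "5) empty mind (not focused, without any particular thoughts".

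In the same section the KSS is an ordered rating from 1 to 9: "Participants are required to rate their ability to maintain wakefulness on a Likert scale".

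Under Secondary Outcome Measures, subjective sleepiness is assigned to the KSS and mind wandering to the CEC, and then: "The outcome measure for both is the score on the corresponding scale".

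Two later statements bear on how that score would be handled. Statistical Analysis gives means for continuous variables and percentages for categorical ones, without placing the CEC in either group. OSS Criteria Accuracy Evaluation describes the study's data as continuous values, counts or proportions, and names no nominal or ordinal type.

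**The concern.** An outcome called a mind-wandering score should rise when mind wandering rises. The CEC code does not do this. The only option that is the named construct has code 4, and a different state, an absence of thoughts, has the higher code 5. Codes 2 and 3 separate distraction by the task from distraction by the surroundings, which is a difference of source and not of amount.

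The effect of altered sleep on mind wandering is a stated purpose of the testing (Experimental Timeline), and mind wandering is a named secondary outcome in the Abstract. If the code is analysed as it is defined, like the KSS, sleep loss that moves people from wandering thoughts to an empty mind would appear as an increase in the mind-wandering outcome, and opposite moves between options could cancel. The result could have the wrong direction or be missed.

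**Working it through.** The plan gives no figure on this point, so there is nothing to reproduce. The option codes 1-5 come from Description of the Tests. All category shares below are assumptions chosen to show how the score behaves; none comes from the documents. The mean score is the sum of code × share.

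**Step 1. Can the score move against mind wandering?** Take shares for options 1 to 5:

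- Before: 0.30, 0.10, 0.10, 0.40, 0.10. Mean = 0.30 + 0.20 + 0.30 + 1.60 + 0.50 = 2.9.
- After: 0.30, 0.10, 0.10, 0.10, 0.40. Mean = 0.30 + 0.20 + 0.30 + 0.40 + 2.00 = 3.2.

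Mind wandering falls by 30 percentage points and the score rises by 0.3. In general, moving a share *p* from option 4 to option 5 raises the mean by *p* × (5 − 4) = *p*.

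**Step 2. Can mind wandering change without the score moving?** Move 20% of ratings from option 3 to 4 and 20% from option 3 to 2. The mean changes by 0.20 × (+1) + 0.20 × (−1) = 0, while mind wandering rises by 20 points.

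**Step 3. Does one score correspond to one state?** A mean of 3.0 arises from:

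| Assumed shares | Mean | Mind wandering |
|---|---|---|
| 100% option 3 | 3.0 | 0% |
| 50% option 1, 50% option 5 | 0.5 × 1 + 0.5 × 5 = 3.0 | 0% |
| 1/3 option 1, 2/3 option 4 | 1/3 × 1 + 2/3 × 4 = 3.0 | 67% |

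**Step 4. Does the numbering matter if a coarse order of focus is granted?** Compare shares (0.40, 0.30, 0.10, 0.15, 0.05) with (0.50, 0.05, 0.10, 0.10, 0.25). The differences by option are +0.10, −0.25, 0, −0.05, +0.20. Keep focused below distracted (options 2, 3) below not focused (options 4, 5), and change only the order within each pair:

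- As coded: 0.10 − 0.50 + 0 − 0.20 + 1.00 = +0.40.
- 2 and 3 swapped: 0.10 − 0.75 + 0 − 0.20 + 1.00 = +0.15.
- 4 and 5 swapped: 0.10 − 0.50 + 0 − 0.25 + 0.80 = +0.15.
- Both swapped: 0.10 − 0.75 + 0 − 0.25 + 0.80 = −0.10.

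So even with the coarse order kept, the sign of the difference can depend on the numbering within the pairs. If all 24 numberings of options 2-5 are allowed, it runs from −0.95 to +0.45. Throughout, mind wandering itself falls from 15% to 10%.

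**The case against.** The strongest reply is that no faulty analysis is written down. A reader might infer from the word score that the plan commits to averaging the CEC or fitting a linear model to it. The documents do not support that: no section states a mean, slope or linear model for the CEC. Percentages are provided for categorical variables, proportions are among the recognised data types, and the generalized linear mixed model named for the first main objective belongs to a class that includes a binomial model. The analysis of a secondary self-report item is also commonly left to a statistical analysis plan, which is not shown.

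A reader might also infer that the five codes are pure labels with no order. That goes too far. The item is introduced as a rating of focusing level, and an order of focused, distracted, not focused can be defended.

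Both replies stand, and they limit the point. They do not remove it. The article does fix the outcome variable, and an analysis plan that follows it inherits the definition. The CEC is nowhere classed as categorical and is paired with an ordered scale. The coarse order does not rank option 2 against 3 or option 4 against 5, and it would make the score an index of lost focus, whereas the article labels it mind wandering.

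**Conclusion.** The point holds as a fault in an outcome definition. As written, the 1-5 CEC score does not measure mind wandering, because the construct is one category and a different category is coded above it. That conclusion rests only on the option descriptions and the outcome sentence. The sizes shown, such as a 0.3 rise in score while mind wandering drops by 30 points, rest on assumed shares; they show what can happen and do not predict the trial's data.

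Severity is low. The CEC is a secondary outcome in a study that the article calls exploratory, and neither main objective, the primary outcome nor the sample size depends on it.

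**What to change.** In Secondary Outcome Measures:

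- Keep the word score for the KSS only, and state that the CEC is categorical.
- Define the mind-wandering outcome as option 4, yes or no.
- Report the proportions of all five options per test block, in line with the rule for categorical variables under Statistical Analysis.
- Analyse the yes/no outcome with a binomial mixed model with participant as random effect.
- Label any other grouping, such as options 4 and 5 together, as a sensitivity analysis.

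The article reports database lock in June 2025 with analysis under way, so the choice of category should be recorded with its date, and before the CEC results are examined if that is still possible. Otherwise the grouping could be chosen after seeing the data.

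The cost is a few sentences; no new data or change of procedure is needed. The downside is that a yes/no outcome carries slightly less information than a truly ordered scale would.

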### Data Analysis

#### Statistical Analysis

The analyses will be performed using R version 4.4.2 (R Foundation for Statistical Computing) and IBM SPSS Statistics version 27 (IBM Corp) software for Windows. The normality of the data will be assessed using the Shapiro-Wilk normality test, the equality of variance will be evaluated with the Levene test, and the sphericity of the data will be checked using the Mauchly test. Continuous variables will be expressed as means and categorical variables as proportions (%). *P* values less than .05 will be considered statistically significant.

#### OSS Criteria Accuracy Evaluation

Considering that the collected data consist of either continuous linear data, counts, or proportions, it is very likely that some of the data will not follow a normal distribution. Therefore, the use of parametric tests may be compromised. Moreover, our outcomes are measured repeatedly over time and may be highly dependent on interindividual variability. Thus, we will use a generalized linear mixed model to explore our first main objective, with relevant interindividual data incorporated into the model if needed (including patient ID, age, gender, daydreaming frequency, chronotype, and sleep history).

Using such models, OSS and MWT sleep onset latencies will be compared over time in order to determine whether OSS criteria can accurately detect drowsiness compared to the MWT.

As a second step, behavioral performance based on the OSS score will be assessed to determine whether instantaneous drowsiness states, identified by OSS, can detect momentary functional impairments. The evaluation of OSS temporal accuracy will be conducted by selecting OSS scores greater than 0 at a time T (20-second epoch), surrounded by lower score values (at T-20 seconds and T+20 seconds) [26]. Behavioral outcomes will then be compared using a generalized linear mixed model between T-20 seconds, T, and T+20 seconds of selected OSS scores.

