## Methods

### Objectives

This study has 2 main objectives. This study’s first aim is to determine whether the OSS criteria can accurately detect manifest sleepiness, compared to the MWT, and to evaluate its temporal accuracy in detecting drowsiness-induced momentary behavioral outcomes, including driving performance, vigilance, and sustained and selective attention.

Second, this study aims to validate robust models based on a multimodal EEG index, derived from resting-state activity during bio-calibration, for predicting functional impairments linked to drowsiness, particularly in driving performance, vigilance, sustained, and selective attention.

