### Participants

#### Sample Size Calculation

This study is exploratory, since, to our knowledge, no other study has used the OSS to predict manifest sleepiness. Thus, because no data would allow us to statistically determine the number of participants required, this number has been arbitrarily set to 40 healthy volunteers. We believe this number will facilitate preliminary exploration at both inter- and intraindividual levels with an appropriate protocol.

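### A latency comparison at P<.05 estimates bias between OSS and MWT but does not by itself establish trial-level agreement or detection accuracy

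*Protocol article*

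**What the plan says.** Under Objectives, the protocol article says that the "first aim is to determine whether the OSS criteria can accurately detect manifest sleepiness, compared to the MWT". Under OSS Criteria Accuracy Evaluation it states that "we will use a generalized linear mixed model to explore our first main objective", and then that "OSS and MWT sleep onset latencies will be compared over time in order to determine whether OSS criteria can accurately detect drowsiness". The general Statistical Analysis section supplies the only criterion: P "values less than .05 will be considered statistically significant".

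The two latencies are defined in different places and mark different events:
- **OSS latency** (Primary Outcome Measure) runs from lights out to the first 20-second epoch scored 3 or 4.
- **MWT latency** (Secondary Outcome Measures) runs from lights out to the first epoch of any sleep stage. It is set to 40 minutes if the participant stays awake throughout.

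Description of the Tests adds that an MWT trial is stopped once unequivocal sleep is seen. The OSS is scored both by a trained experimenter and by the MEEGAWAKE algorithm. Accuracy, precision, recall and F1 are named only for the resting-state EEG classifiers.

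On status, the Sample Size Calculation section says "This study is exploratory, since, to our knowledge, no other study has used the OSS to predict manifest sleepiness", and that "this number has been arbitrarily set to 40 healthy volunteers".

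**The concern.** The question is one of accuracy against a reference, but the named analysis is a comparison of latencies with a significance threshold. These are different questions. Two methods can have equal average latencies and disagree widely on individual trials. Two methods can also track each other almost perfectly and differ by a small, constant and highly significant amount.

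This is more than detail left to an analysis plan, because the article states both the analysis and the conclusion to be drawn from it. It matters because the OSS score is the primary outcome, the stated aim is validation, and Clinical Health Applications suggests automatic OSS latency during the MWT for managing sleepy patients. A reader given only a P value could not tell how far an OSS latency may lie from the MWT latency on a given trial.

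**Working it through.** **The plan's own figure.** The sample size of 40 is set without a power calculation, SD or margin, so there is nothing to reproduce.

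**Number of paired trials.** Session 1 has 3 test blocks; session 2 has 6 and then 3. That makes 3 + 6 + 3 = 12 blocks. Assuming one MWT per block, 40 × 12 = 480 paired trials.

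**What the test can flag.** The mean difference detectable with 80% power at two-sided .05 is (1.96 + 0.84) × SD / √n, where SD is that of the OSS − MWT differences. The documents give no SD, so a range is assumed. Taking n = 480 treats all trials as independent; n = 40 treats the differences as fully shared within a participant. The truth lies between. The limits of agreement are the bias ± 1.96 × SD.

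| Assumed SD (min) | Detectable, n = 480 (min) | Detectable, n = 40 (min) | Limits around bias (min) |
|---|---|---|---|
| 1 | 0.13 | 0.44 | ±1.96 |
| 5 | 0.64 | 2.21 | ±9.8 |
| 10 | 1.28 | 4.43 | ±19.6 |

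The closer the agreement, the smaller the offset that is declared significant. Conversely, if the true mean difference is zero, a valid test at .05 is non-significant in 95% of studies whatever the SD, so the P value says nothing about the last column.

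**Significance against agreement.** A simulation of 40 × 12 trials (2,000 replicates) assumed MWT block means falling from 32 to 10 minutes, between- and within-participant SDs of 6 minutes, and latencies held to 0.5–40 minutes. The method effect was tested with Gaussian equivalents of a random-intercept model and of a model with a participant-level method effect.

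| OSS latency | Significant, random intercept | Significant, participant-level method effect | Concordance | Limits of agreement (min) |
|---|---|---|---|---|
| MWT − 0.5 min, noise SD 0.5 | 0% | 100% | 0.998 | −1.5 to +0.5 |
| MWT − 1 min, noise SD 0.5 | 100% | 100% | 0.994 | −2.0 to 0.0 |
| MWT − 10 min, noise SD 5 (mean difference −8.9 after truncation) | 100% | 100% | 0.63 | −18.6 to +0.7 |

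The second and third rows get the same verdict from the test, although one shows close agreement and the other does not. In the first row the verdict changes with the random-effects structure while agreement stays the same. The estimated bias and the limits separate the cases; significance does not.

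**If the model relates one latency to the other.** The article gives no equation, so this reading is open. A significant slope would show association. With the same assumed block means (steps of 2 minutes over 12 blocks), the between-block variance is 4 × (144 − 1)/12 = 47.7. The variance within blocks is 36 + 36 = 72. Two latencies sharing nothing but this time course would have a pooled correlation of about 47.7/(47.7 + 72) = 0.40. Adjusting for block removes that source, but the slope still measures association and not accuracy.

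**The case against.** Several points on the other side stand.

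- **Bias is informative.** The mixed model estimates systematic bias, and its course over time if a time interaction is fitted. A large bias would be evidence against accuracy. A reader might infer that the planned analysis can say nothing either way; that goes too far. What fails is significance as the yardstick.
- **The model is not written out.** Comparing average latencies is the natural reading, not the only one. Nor does the article say that a non-significant result will be read as equivalence. A reader might infer such a pass rule, but no text supports it.
- **The stopping rule limits how bad an undetected OSS could be.** A reader might infer that an OSS unrelated to the MWT would almost always come out as no different. Trials end when unequivocal sleep is seen, so OSS latency cannot run far past MWT onset unless trials without OSS onset are given a long value, and no rule for these is stated. An unrelated OSS would therefore tend to look early, and often show a bias.
- **The study is labelled preliminary and exploratory**, its size is admittedly arbitrary, and the model is used to explore the objective. Supporting statistics may sit in an analysis plan that is not shown.

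These points lower the severity. They do not make the named comparison answer the accuracy question, because the article itself ties that conclusion to it.

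**Conclusion.** The point holds in a limited form. The stated comparison estimates bias between OSS and MWT latencies, but by itself it does not establish trial-level agreement or detection accuracy, on either reading of the model. That follows from what a difference test or a slope measures and does not depend on the simulation. The sizes shown do depend on assumed SDs, an assumed latency profile and one MWT per block. A small constant offset is plausible because the two onsets are defined differently; its actual size is unknown from the documents. Given the exploratory label, this should be fixed before the accuracy conclusion is reported, but it does not invalidate the study or its data.

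**What to change.** 1. Keep the mixed model to describe bias over time.
2. Base the accuracy conclusion on paired trial-level agreement from a repeated-measures model with participant random effects: bias with 95% limits of agreement, and an intraclass or concordance coefficient, each with confidence intervals.
3. Add sensitivity and specificity of OSS onset for MWT sleep onset, with intervals clustered by participant.
4. Report manual OSS and MEEGAWAKE separately.
5. State how three kinds of trial are handled: those without OSS onset, those ended early by the stopping rule, and those at the 40-minute ceiling.
6. Judge the limits against an acceptable difference in minutes, fixed before the comparison is run if that is still possible. The Results section reports database lock and the start of analysis in June 2025, so the date on which the difference was set should be reported. If the comparison has already been run, present the agreement estimates descriptively.

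The cost is analysis wording and programming on the same data, with no new measurements. The downside is that the limits may prove wide, or the acceptable difference may not be met.

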Manifest sleepiness [1] is the transformational effect of underlying physiological sleepiness on behavior due to voluntary or involuntary sleep deprivation, circadian misalignment, or pathologies inducing excessive daytime sleepiness. Manifest sleepiness is also referred to as drowsiness, hypoarousal [2], or continuous nonimperative sleepiness [3] by other authors. We will here use the generic term “drowsiness” to qualify manifest sleepiness. Drowsiness is characterized by an inappropriate waking behavior and a lasting inadequate level of arousal, which results in an inability to stay awake, difficulties in maintaining sustained attention and vigilance (ie, brain fog), and affects judgment and decision-making abilities and encourages risk-taking [4]. Drowsiness can thus induce functional consequences in terms of both disability and accident risk [5-7], to the same extent as the effects of alcohol consumption [8]. Drowsiness also redirects attention to thoughts that are not related to the task at hand [9]. This modification in attentional orientation, known as mind wandering, also impacts cognitive performance [9,10]. Finally, introspective sleepiness [1] concerns the individual’s self-assessment of their internal state of sleepiness. Manifest and introspective measures are linked because they both reflect underlying sleep pressure and drowsiness and therefore may arise from the same underlying drive state [11]. However, drowsy people often fail to accurately assess their level of drowsiness and therefore overestimate their ability to make important decisions and perform complex tasks [12], despite their decreased cognitive abilities, which can lead to dangerous consequences. Identifying and measuring real-time drowsiness or predicting it in high-risk situations like working or driving is thus a significant public health challenge [13,14].

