### Outcome Measures

#### Primary Outcome Measure

The primary outcome measure corresponds to the OSS score, which relies on the analysis of electrophysiological variables to assess the instantaneous drowsiness state, corresponding to the participant’s level of sleepiness. The OSS score, ranging from 0 (full alertness) to 4 (very drowsy), is assigned every 20 seconds, based on specific EEG activity (amount of beta, alpha, and theta waves) observed simultaneously in 2 regions of the brain during each epoch, and accompanied by distinct eye blinks and movements (normal or slow). An OSS score of 0 corresponds to continuous beta activity, with no alpha or theta activity and no slow eye movements. In contrast, an OSS score of 4 is characterized by the presence of alpha and/or theta rhythms for more than 10 cumulative seconds, associated with slow eye movements.

The OSS was scored both manually, by a trained experimenter—based on EEG (Fz, Cz, Pz, C4, O2, C3, O1, and P3) and EOG (vertical and horizontal) recordings—and automatically, by the MEEGAWAKE algorithm—based on EEG (Cz and Pz)— every 20 seconds throughout all behavioral tests, to reflect the spontaneous drowsiness states.

The MEEGAWAKE algorithm uses data-driven criteria to cope with interindividual variability. After an initial artifact rejection step relying on detecting both temporal and frequential abrupt variations or nonphysiological behavior, the analysis step aims to determine recording-specific thresholds based on EEG power ratios in the usual frequency bands. In addition to this frequency analysis, a temporal localization of EEG events is performed to analyze burst activity. Based on the results of this analysis, the final step is to classify the 20-second epochs into OSS drowsiness states.

During MWT, sleep onset is defined as the start of the first epoch scored 3 or 4. OSS sleep latency (OSS latency) is defined as the time from lights out until the start of the first epoch scored as 3 or 4 (expressed in minutes).

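### The only stated test of OSS temporal accuracy is a contrast around OSS peaks, which can show time-locking but not how well OSS detects impairment

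*Protocol article*

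**What the plan says.** The Objectives section sets the temporal aim for the OSS: "evaluate its temporal accuracy in detecting drowsiness-induced momentary behavioral outcomes, including driving performance, vigilance, and sustained and selective attention". In OSS Criteria Accuracy Evaluation the second analysis step repeats it as the question whether "instantaneous drowsiness states, identified by OSS, can detect momentary functional impairments".

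The procedure given there has two parts:
- Selection: "selecting OSS scores greater than 0 at a time T (20-second epoch), surrounded by lower score values", the neighbors being the epochs 20 seconds before and after.
- Comparison: "Behavioral outcomes will then be compared using a generalized linear mixed model between T-20 seconds, T, and T+20 seconds of selected OSS scores".

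The same paragraph says in general terms that behavior will be assessed by OSS score, but describes no other procedure for doing so. Under Primary Outcome Measure, "The OSS score, ranging from 0 (full alertness) to 4 (very drowsy), is assigned every 20 seconds", and scoring covers all behavioral tests. The accuracy, precision, recall and F1 measures appear under Predictive Models Using Resting State EEG and belong to those models. No such measure is named for OSS against behavior.

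**The concern.** The aim is worded as detection, but the procedure starts from the output of the detector. It chooses epochs by their OSS score and asks whether behavior differs between a local peak and its two neighbors. Two things follow.

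First, an epoch inside a run of equal scores cannot be T. The Introduction says: "Drowsiness is characterized by an inappropriate waking behavior and a lasting inadequate level of arousal". The sessions use fragmented sleep and total sleep deprivation to bring this state about, so the rule gives least weight to drowsiness of the persistent kind.

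Second, a detector is judged by how often it misses impaired epochs and how often it raises an alarm in unimpaired ones. Impaired epochs at OSS 0 away from a peak, and OSS>0 epochs that neither form nor flank a peak, are not in the comparison. A clear difference between T and its flanks could be reported as temporal accuracy while the miss and false-alarm rates remain unknown.

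**Working it through.** The document gives no figure to reproduce here, so the rule itself was checked in three ways.

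**1. Which three-epoch patterns qualify.** Inputs: five levels (0-4) and the selection rule above. There are 5 × 5 × 5 = 125 patterns. For a score b at T, each neighbor can take b values (0 to b-1), giving b² patterns.
- Qualifying: 1 + 4 + 9 + 16 = 30.
- Both neighbors above 0, (b-1)² each: 0 + 1 + 4 + 9 = 14.
- At least one neighbor at OSS 0: 30 - 14 = 16. Both at 0: 4.
- All three epochs at level 3 or 4: one pattern, 3-4-3.

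So peaks inside a longer drowsy spell qualify, and OSS-0 epochs do enter as flanks. A constant run never supplies T.

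**2. What share of OSS>0 epochs can serve as T.** Assumption: a score stays the same in the next epoch with probability s. Otherwise it moves either one level (step chain) or to any other level with equal chance (jump chain).
- Step chain: the long-run shares of levels 0-4 are 1/8, 2/8, 2/8, 2/8, 1/8. Levels 1-3 are peaks with probability (1-s)²/4 and level 4 with probability (1-s)². The share is [(6/8)(1-s)²/4 + (1/8)(1-s)²] / (7/8) = (5/14)(1-s)².
- Jump chain: all levels are equally common, and level b is a peak with probability b²(1-s)²/16. The share is (30/4)/16 × (1-s)² = (15/32)(1-s)².

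| s | Step | Jump |
|---|---|---|
| 0.3 | 17.5% | 23.0% |
| 0.5 | 8.9% | 11.7% |
| 0.7 | 3.2% | 4.2% |
| 0.8 | 1.4% | 1.9% |
| 0.9 | 0.4% | 0.5% |

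Simulated chains of 400,000 epochs agree to within 0.2 percentage points. Counting OSS>0 epochs that enter either as T or as a flank, the same two chains (summed exactly over five-epoch windows) give 43-50% at s = 0.3, 23-26% at 0.5 and 8-10% at 0.7. Either way the share falls as persistence rises.

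**3. Whether the contrast fixes sensitivity and specificity.** Take 1,000 hypothetical epochs, with OSS>0 counted as a detection:
- 100 peaks, 25 impaired (25%);
- 200 flanks at OSS 0, 20 impaired (10%);
- 200 unselected epochs with OSS>0;
- 500 unselected epochs at OSS 0.

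The planned contrast is 25% against 10% in both cases below. Only the unselected epochs differ.
- Case A, 60% of the 200 and 2% of the 500 impaired: sensitivity (25 + 120)/(25 + 120 + 20 + 10) = 145/175 = 83%; specificity (180 + 490)/(180 + 490 + 75 + 80) = 670/825 = 81%.
- Case B, 10% and 20% impaired: sensitivity (25 + 20)/(25 + 20 + 20 + 100) = 45/165 = 27%; specificity (180 + 400)/(180 + 400 + 75 + 180) = 580/835 = 69%.

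The same planned result is compatible with a good detector and a poor one.

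**The case against.** The best defense is that the contrast fits the words momentary and temporal. Comparing before, peak and after within one event is self-controlled, so it is less exposed to time-on-task and circadian drift than a model over all epochs. It follows a cited earlier study, and the trial calls itself exploratory. This stands: the peak contrast is a legitimate test of time-locking and should stay. It does not supply the detection result that the section asks for.

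Several stronger readings are tempting, but the document does not support them:
- A reader might infer that all sustained drowsiness is excluded. Neighbors need only be lower, so a 3-4-3 peak inside a long spell qualifies. So do plateau epochs next to a peak, as flanks.
- A reader might infer that OSS-0 epochs never enter. Sixteen of the 30 qualifying patterns have at least one.
- A reader might want one fixed figure for the drowsy epochs lost. The share depends on persistence, which the document does not report, and on whether flanks are counted.
- A reader might take "with relevant interindividual data incorporated into the model if needed (including patient ID" to mean that clustering by participant could be ignored. The section chooses a mixed model because outcomes are repeated and vary between people. The exact random effects are detail for an analysis plan.
- A reader might extend the point to all OSS accuracy work. The first step, OSS latency against MWT latency, does not use peak selection.

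**Conclusion.** The point holds in this limited form. The one procedure stated for OSS temporal accuracy tests whether behavior changes around strict local OSS peaks. Because epochs are chosen on OSS, it does not identify sensitivity, specificity or false alarms, and so does not alone answer the detection question. That conclusion follows from the rule and needs no assumption about the data.

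The size of the selection is illustrative only. The percentages rest on two simple chains and assumed persistence; what is robust is the direction, namely that more persistent drowsiness leaves a smaller share to analyze. The change is worth making, but the gap does not invalidate the planned contrast.

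**What to change.** Keep the peak contrast and name it the time-locking analysis. Add a mixed model on all 20-second epochs of each behavioral test:
- outcome: behavior in the epoch; predictor: OSS level (0-4) of the same epoch;
- random effect for participant, terms for time-on-task and block, and allowance for serial correlation;
- sensitivity and specificity (or AUC) of OSS against an epoch-level impairment defined before this analysis is run, for example at least one PVT lapse, omission or line crossing in the epoch, with intervals clustered by participant.

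The Results section puts database lock in June 2025 with analysis under way, so date the addition and label it as made after lock. If it is not added, limit the conclusion to time-locking around OSS peaks.

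Cost: analysis wording and computing time. OSS is already scored on every epoch of the behavioral tests, and the planned contrast already needs behavior by 20-second epoch. For driving alone, 20 minutes × 3 epochs = 60 per drive; 12 blocks (3 in session 1, 6 + 3 in session 2) give 720 epochs per participant, or 28,800 for 40 participants before any losses.

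Downside: serial correlation must be modeled, and each epoch holds few responses. With PVT intervals of 2 to 10 seconds, ignoring response time, an epoch holds between 20/10 = 2 and 20/2 = 10 stimuli, so epoch-level impairment will be a coarse measure.
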